#### Analysis Plan

The primary analyses will employ manual stepwise logistic regressions. Specifically, dependent measures will be 30 day point prevalence abstinence at 6-month follow-up and 7 day point prevalence abstinence at 8-week follow-up. Separate logistic regression analyses will be conducted for each time point (validated by saliva cotinine sample). In the primary analyses, subjects lost to follow-up will be assumed to be active smokers. In Step one of the logistic regression, experimental condition will be entered as a dummy coded variable (0 = control condition; 1 = experimental condition). This step will test the primary hypothesis regarding the impact of sending free NRT on quit rates. Steps two and three of the logistic regression will involve adding interaction terms to test the mediator and moderator hypotheses (3-HC/cotinine ratio, compliance with NRT use, prior use of NRT; main effects terms entered in Step two and interaction terms entered in Step three). Sex difference analyses will be conducted in a similar manner (i.e., is there an interaction effect of subjects' sex by receipt of NRT on abstinence rates at 6-month follow-up?). As part of these primary analyses, we will also conduct a chi-square test to explore whether there is differential loss to follow-up between experimental conditions. Further we will replicate the primary analyses with all subjects with missing data excluded from the analyses. If the results are the same between the analyses where the missing data is excluded and where subjects lost to follow-up are assumed to still be current smokers, then we can safely assume that there is no differential attrition between conditions (or, at least none that impacted on the outcome of the trial).

Subgroup analyses will examine quit rates among subjects within the experimental and control conditions who: (a) are slow versus fast nicotine metabolizers as measured by the 3-HC/cotinine ratio; (b) report using all 5 weeks of the free NRT they were sent as compared with those who do not use all 5 weeks; (c) had used NRT for a quit attempt at least once before participation in the proposed study as compared with those who had never used NRT before; and (d) are male or female (to assess any interaction by sex). Further, we will compare subjects in the experimental condition who used the NRT to just those subjects in the control condition who did not use any NRT during the same time period (i.e., they did not obtain NRT from other sources). Finally, using just the baseline data (N = 1,000), we will relate the 3-HC/cotinine ratio to patterns of smoking and prior use of NRT.

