#### Content of Baseline Interview

The primary purpose of the baseline interview is to assess eligibility for the randomized controlled trial. Specifically, subjects will be asked of their interest in receiving free NRT, its use within one week of receipt, and health contraindications for NRT use. In addition, other questions will also investigate the following: a) subjects' heaviness of smoking [21], b) number and duration of past quit attempts, c) past use of NRT, d) current life stressors, e) motivation to quit smoking, f) past and present drug use, g) level of alcohol intake (AUDIT-C) [22], h) presence of mental health disorders diagnosis, and e) a series of demographic characteristics such as age, gender, ethnicity, marital status, education and employment status.

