### Randomization

Recruitment is conducted using a Random Digit Dialing survey with computer assisted telephone interview (CATI) technology. At the end of the baseline interview, eligible subjects will be allocated to experimental and control conditions using a simple randomization without replacement built into the CATI program (no stratification or minimization given the large proposed sample size in this trial).

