### Data Analysis

#### Power analysis

Quit rates for those who use nicotine patches have been obtained from several sources, including systematic reviews by Fiore et al. [26] and a Cochrane review by Stead and colleagues [16]. Both these reviews indicate a 10% increase in tobacco cessation rates upon using nicotine patches as compared to placebo at 6-month follow-up. This 10% increase is roughly in concordance with the 30 day point prevalence rate for abstinence observed at the 6-month follow-up point of the STOP mass distribution demonstration trial (9%; note that this trial had no control group so the results reflect pre-post changes in smoking rates) [12]. However, we recognize that both of these estimates are probably too large for a pragmatic randomized controlled trial because the impact of interventions is often smaller in real world settings (and pre-post estimates, such as those found in the STOP Study, can also be inflated). Thus, we have chosen to power our trial based on the assumption that our quit rate will be half as large (i.e., a 5% increase in quit rates in the experimental condition versus the control at 6-month follow-up). Finally, we can estimate a 3.7% baseline rate of smoking cessation at 6-month follow-up in a general population sample using findings from the 2008 Canadian Tobacco Use Monitoring Survey (CTUMS) [3]. Given these results, we predict that the subjects in the control condition will display a 3.7% quit rate and subjects in the experimental condition will display a 8.7% quit rate at 6-month follow-up.

Using these assumptions, a power analysis was conducted; this indicated that a total of 403 respondents would be needed per condition to detect a 5% difference at a significance level of .05 with a power of 80% (estimate calculated with continuity correction factored in) [27]. Thus, we have chosen an ideal sample size of approximately 800 respondents in order to conduct appropriate analyses.

Based on our previous research using a similar research design, albeit with problem drinkers rather than smokers [28,29], a 20% attrition between baseline and 6-month follow-up can be expected (the most important follow-up for this study); this would mean that a sample size of 1,000 respondents would be needed at baseline to take part in the randomized trial. Similar follow-up rates have been obtained for smokers in the Ontario Tobacco Survey, indicating that a 20% attrition rate estimate is also reasonable for smokers [30].

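### The primary model contains condition only; prespecifying two or three baseline interview covariates would be a small, optional gain in efficiency

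*Protocol article*

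**What the plan says.** All references are to the protocol article.

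- **Analysis Plan.** The primary analysis is a logistic regression built in steps. In Step one "experimental condition will be entered as a dummy coded variable", and this step is the test of the primary hypothesis. Steps two and three add main effects and then interactions for the 3-HC/cotinine ratio, compliance and prior NRT use. Their stated purpose is to test mediator and moderator hypotheses, not to adjust the primary comparison. Subjects lost to follow-up count as smokers.
- **Content of Baseline Interview.** The items include "heaviness of smoking [21], b) number and duration of past quit attempts", and also motivation to quit.
- **Randomization.** Allocation takes place when the baseline interview ends, by simple randomisation with "no stratification or minimization given the large proposed sample size in this trial".
- **Validation of self-report by saliva cotinine samples.** The baseline saliva kit is mailed some days after the interview, and so after allocation.
- **Power analysis.** The sample size rests on an unadjusted comparison of two proportions.

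**The concern.** Three variables that plausibly bear on quitting are in hand for every randomised subject before allocation, at no extra cost in data collection. Neither the randomisation nor the primary model uses them.

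Two things follow. If the variables do predict quitting, leaving them out gives up some power. And if the arms happen to differ on them, the headline estimate carries that difference uncorrected. The number of subjects is large but the number of events is not: about 50 quitters are expected under the plan's own assumptions and its missing-outcome rule.

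**Working it through.** **1. Reproduce the planned sample size.** Inputs from Power analysis: "subjects in the control condition will display a 3.7% quit rate and subjects in the experimental condition will display a 8.7% quit rate"; alpha .05; power 80%; "estimate calculated with continuity correction factored in". Sidedness is not stated; two-sided reproduces the figure.

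Uncorrected n per arm = [1.960 × √(2 × 0.062 × 0.938) + 0.842 × √(0.037 × 0.963 + 0.087 × 0.913)]² / 0.05² = (0.668 + 0.285)² / 0.0025 ≈ 364.

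With continuity correction: n/4 × [1 + √(1 + 4/(n × 0.05))]² = 91.0 × (1 + 1.104)² ≈ 403.

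This matches "a total of 403 respondents would be needed per condition". The article rounds to about 800 in total and, because "a 20% attrition between baseline and 6-month follow-up can be expected", raises it to 800/0.8 = 1,000, or 500 per arm.

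**2. Rates under the missing = smoker rule.** Control 0.8 × 3.7% = 2.96%; experimental 0.8 × 8.7% = 6.96%. This assumes that loss is unrelated to arm and to quitting. Expected quitters: 500 × 0.0296 = 14.8 and 500 × 0.0696 = 34.8, about 50 in all.

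**3. Power of the planned unadjusted test (two-sided, no continuity correction).** At 500 per arm, 2.96% v 6.96%:

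z = [0.04 − 1.960 × √(2 × 0.0496 × 0.9504 / 500)] / √[(0.0296 × 0.9704 + 0.0696 × 0.9304) / 500] = (0.0400 − 0.0269) / 0.01367 = 0.957, so power is 83.1%.

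The same calculation gives 83.9% for 403 per arm at 3.7% v 8.7%, and 90.7% for 500 per arm with no loss.

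**4. Gain from adjustment.** Simulation with 6,000 trials per cell: logistic Wald test at two-sided 0.05, condition only against condition plus three baseline covariates, marginal quit rates held fixed. Covariate strength is an assumption, set by the SD of the covariates' combined linear predictor. The gain is in percentage points.

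| Setting | SD 0 (AUC 0.50) | SD 0.4 (AUC 0.61) | SD 0.7 (AUC 0.69) | SD 1.0 (AUC 0.76) |
|---|---|---|---|---|
| 500 per arm, 2.96% v 6.96% | +0.1 | +0.4 | +1.0 | +2.2 |
| 403 per arm, 3.7% v 8.7% | −0.3 | +0.1 | +0.9 | +2.7 |
| 500 per arm, no loss | −0.2 | +0.1 | +0.6 | +1.1 |

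In the first row the strongest case moves power from 82.7% to 84.9%. Each single power estimate has a simulation error of about √(0.83 × 0.17 / 6,000) = 0.5 points; the paired gains are less noisy. The small negative entries, where the covariates predict nothing, are not evidence of a real loss.

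**5. Chance imbalance.** With 500 per arm, the standardised difference between arms in any covariate has an SD of √(2/500) = 0.063. A further simulation (8,000 trials per setting, one prognostic score, 2.96% v 6.96%) looked at the roughly 16% of trials in which chance puts the experimental arm at a disadvantage of at least one such SD:

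- score coefficient 0.7 (AUC about 0.69): power 76.9% unadjusted, 85.3% adjusted;
- score coefficient 1.0 (AUC about 0.76): power 76.8% unadjusted, 86.9% adjusted.

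When chance favours the experimental arm, unadjusted power is 88.5% and 90.3%, against 85.0% and 86.2% adjusted. These subset figures have an error of about 1 point.

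**6. Effect on the odds ratio.** At 2.96% v 6.96% the marginal odds ratio is 2.45. The conditional odds ratio is 2.47, 2.51 and 2.58 at SD 0.4, 0.7 and 1.0.

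**The case against.** The strongest reply is that nothing here is wrong. An unadjusted comparison is valid under simple 1:1 randomisation, agrees with the sample size calculation and answers the pragmatic question directly. Chance imbalance is already allowed for in the type I error and the confidence interval, and with 500 per arm any one imbalance is usually slight. An adjusted supporting model may also sit in an analysis plan that is not shown. All of this stands, and it is why the point is only an optional improvement. It does not remove the point, because the article states the primary model in full.

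Four stronger readings are tempting, and the document does not support them.

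- *The omitted variables are strong predictors.* The article gives no figure for this. Eligibility also narrows their range: at least 10 cigarettes a day, and willing to start patches within a week in order to quit. Weak prediction is plausible, and the gain is then close to zero.
- *The trial is short of power without adjustment.* It is not: about 83% in the least favourable of the settings above, against a target of 80%.
- *The unadjusted result is biased.* Chance imbalance is random error, not bias. Adjustment removes some of that error from the particular trial that is run.
- *The gain is free.* Data collection costs nothing extra, but the odds ratio becomes conditional, and covariate coding and handling of missing values must be settled in advance.

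**Conclusion.** The point holds as an optional gain in efficiency. The planned primary test is valid and reaches its power target. Adding a few interview covariates would raise power by about 0 points if they predict weakly, about 1 point at a combined AUC of about 0.69, and 2 to 3 points at about 0.76 (1.1 points if nobody is lost). It would also correct chance imbalance in those variables.

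These sizes rest on assumed predictive strength, on the planned quit rates and 20% loss, and on a correctly specified covariate model. The facts about the model, the randomisation and the timing of the interview rest on the text alone.

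**What to change.** Define Step one as condition plus two or three named interview covariates: heaviness of smoking, motivation to quit and number of past quit attempts. Fix their coding and the handling of missing values before any outcome is examined by condition. Stop at three: with about 50 quitters and four coefficients besides the intercept, there are about 50/4 = 12 events per coefficient.

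Report a standardised risk difference with the odds ratio, so that the effect is also given on the absolute scale used for planning. Give the unadjusted comparison as supportive.

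Do not adjust for compliance, which arises after randomisation, or for the 3-HC/cotinine ratio, whose kit is mailed after allocation and whose samples may be incomplete. Both can remain in the secondary steps.

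The cost is a sentence or two in the analysis plan, with no new data and no additional subjects. The small downside is that the odds ratio becomes conditional, which the standardised risk difference addresses.

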## Methods/design

### Design

This is a single-blind, randomized controlled trial of mass distribution of free Nicotine Replacement Therapy to Canadian smokers. A two-stage recruitment process will be employed, in the context of a general population survey with two follow-ups (8 weeks and 6 months). Random digit dialing of Canadian home telephone numbers and an initial interview will identify households with adult (age 18 or over) smokers who smoke 10 or more cigarettes a day. One individual from each household who is willing to take part in a smoking study that involves three interviews, with saliva collection for 3-HC/cotinine ratio measurement at baseline and saliva cotinine verification at 8-week and 6-month follow-ups will be randomly selected (according to most recent birthday). Willing participants will be offered a $20 honorarium for completing the baseline and each of the 8-week and 6-month follow-ups. Verbal consent will be obtained as the initial contact is by telephone.

As part of the baseline survey, eligible subjects will be identified for the second stage of the recruitment process and will be randomized into experimental and control conditions to receive versus not receive nicotine patches. Eligibility will be determined by a series of questions regarding hypothetical interest in nicotine patches to quit smoking (including willingness to have nicotine patches sent to their home) and having no contraindications for using NRT. A randomized half of the eligible subjects will be assigned to the experimental condition and asked for their permission to have nicotine patches sent to their home. These subjects will have 5 weeks of nicotine patches sent to their homes to help them quit smoking. Subjects in the control condition will not be offered nicotine patches. Only subjects in the randomized controlled trial will be followed-up at 8 weeks and 6 months. See Figure 1 for a CONSORT diagram of the proposed study design.

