#### Content of 8-week and 6-month follow-up interviews

At 8-week and 6-month follow-ups, subjects who have not quit will be asked how many cigarettes per day they currently smoke and their intentions to quit smoking; how soon after waking they smoke their first cigarette; and if, since their baseline interview, they have stopped smoking for even one day because they were trying to quit. Subjects in the experimental condition will be asked to evaluate their experiences with NRT and to elaborate on their efforts to quit smoking. Specifically, at 8-weeks subjects will be asked if they received the NRT; how soon after receipt they began to use it; how much of it (if any) they used; if relevant, why they did not use any or all of it; whether or not they experienced any withdrawal symptoms and which ones; and what challenges they encountered to quitting/reducing. At 6-months, subjects will be asked whether or not they purchased additional NRT to help in their quit effort (what type and how much); whether or not they plan to purchase more NRT to quit or maintain their non-smoking; if they have smoked in the past 30 days or reduced from baseline, what benefits they have noticed; what supports they had for quitting; and what additional resources they sought to help them quit. These questions will be asked after the core smoking status outcome measures have been assessed. Subjects in the control condition will also be asked about their use of NRT but the questions will be framed to reflect purchase of NRT from sources other than this ongoing study. Subjects in both conditions will also be asked about their use of other smoking cessation aids.

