#### Secondary outcome measures

Secondary outcome measures are: (1) 7 day point prevalence of smoking abstinence at 8 weeks post-baseline; (2) reduction in smoking since baseline; (3) compliance with the full 5-week course of nicotine patches provided to experimental condition; (4) challenges with quitting/reducing smoking; and (5) purchase and use of NRT and smoking cessation aids at follow-up periods.

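### Compliance is defined only for the experimental arm, yet enters the two-arm logistic model as a main effect and an interaction: the interaction is inestimable and the Step two condition coefficient stops measuring the offer (the primary Step one test is unaffected)

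*Protocol article*

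**What the plan says.** All references are to the protocol article.

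- **Model.** Under Analysis Plan, Step one is condition alone: "experimental condition will be entered as a dummy coded variable (0 = control condition; 1 = experimental condition"). Of that step the plan says "This step will test the primary hypothesis regarding the impact of sending free NRT on quit rates". The later steps involve "adding interaction terms to test the mediator and moderator hypotheses (3-HC/cotinine ratio, compliance with NRT use, prior use of NRT"), with "main effects terms entered in Step two and interaction terms entered in Step three".
- **Definition of compliance.** Secondary outcome measures lists "compliance with the full 5-week course of nicotine patches provided to experimental condition". Subgroup (b) in the Analysis Plan concerns those who "report using all 5 weeks of the free NRT they were sent as compared with those who do not use all 5 weeks". Its lead-in, shared by subgroups (a) to (d), speaks of subjects in both conditions.
- **Control arm.** Under Design: "Subjects in the control condition will not be offered nicotine patches". Under the content of the follow-up interviews, controls are asked about NRT, but "the questions will be framed to reflect purchase of NRT from sources other than this ongoing study".
- **Timing.** The same section has experimental subjects report at 8 weeks how much of the supplied NRT they used, so compliance is a self-report made after randomisation.

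**The concern.** A condition-by-compliance term needs compliance to vary in both arms. Here it can vary in only one, and the plan neither gives controls a value nor confines the analysis to the experimental arm. This is a stated model that conflicts with the document's own definition of a variable, so it is not a detail left to an unseen analysis plan.

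There is a second problem even where the model can be fitted. Compliance follows randomisation and plausibly reflects the wish to quit. Once it is in the model, the condition coefficient no longer compares the groups as randomised, although the Experimental condition section commits to intention to treat.

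Third, the plan speaks of testing mediator and moderator hypotheses with interaction terms. A product term addresses moderation. Compliance is the only listed variable that could mediate, and it gets no mediation analysis.

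At stake is a declared aim (how compliance affects quitting, under Aim of the study) and the reading of the Step two output, which the plan places within its primary analyses.

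**Working it through.** **1. The plan's own figure.** Inputs from Power analysis: 3.7% versus 8.7%, significance level .05, power 80%, continuity correction. Sidedness is not stated; two-sided is assumed.

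n = [1.96·√(2·0.062·0.938) + 0.8416·√(0.037·0.963 + 0.087·0.913)]² / 0.05² = 364.

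With the correction: (364/4)·[1 + √(1 + 4/(364·0.05))]² = 403. This matches the stated 403 per condition. Nothing below changes it.

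**2. Can the terms be estimated?** Let T = condition, C = compliance, M = 3-HC/cotinine ratio, P = prior NRT use.

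- *Controls coded C = 0.* When T = 0, T·C = 0 = C. When T = 1, T·C = C. The two columns agree in every row, whether C is full course yes/no or weeks used. Step three has 8 columns (1, T, M, C, P, T·M, T·C, T·P) and a numerical check at N = 1,000 gives rank 7. Without T·C it has 7 columns and rank 7, so T·M and T·P can still be estimated.
- *Controls coded missing.* Every control is dropped and T = 1 throughout. Step two has 5 columns and rank 4, so there is no condition effect. Each product with T then equals its main effect, so no interaction can be estimated.

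**3. What the Step two condition coefficient measures (controls coded 0).** With T and C (full course yes/no) in the model, the T coefficient is the contrast at C = 0: experimental non-compliers against all controls. M and P adjust that contrast but do not change its nature.

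Step one at the planned rates: OR = (0.087/0.913)/(0.037/0.963) = 2.48.

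Step two: OR = [r/(1−r)]/(0.037/0.963), where r is the quit rate in non-compliers. The document does not give r, so a range is assumed:

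| r (assumed) | Step two condition OR |
|---|---|
| 2.0% | 0.53 |
| 3.7% | 1.00 |
| 6.0% | 1.66 |
| 8.7% | 2.48 |

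The two steps agree only if non-compliers quit as often as the whole experimental arm.

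**4. A case with no patch effect.** Assume half the subjects have a favourable trait, that 80% with it and 20% without it comply, and that everyone quits at 3.7% on average.

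- *Quit rates 6.0% with the trait, 1.4% without.* Non-compliers: 0.2·6.0 + 0.8·1.4 = 2.32%. Compliers: 0.8·6.0 + 0.2·1.4 = 5.08%. Condition OR = (0.0232/0.9768)/(0.037/0.963) = 0.62. Compliance OR = (0.0508/0.9492)/(0.0232/0.9768) = 2.25.
- *Quit rates 5.0% and 2.4%.* Non-compliers 2.92%, compliers 4.48%. Condition OR 0.78, compliance OR 1.56.

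All of these should be 1. About 1,500 simulated trials of 1,000 per setting agree:

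| | 6.0% / 1.4% | 5.0% / 2.4% |
|---|---|---|
| Median Step two log OR, condition | −0.50 | −0.27 |
| Rejection, condition | 11% | 5% |
| Median Step two log OR, compliance | 0.80 | 0.45 |
| Rejection, compliance | 32% | 12% |

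Step one stayed centred on zero, with rejection of about 4%.

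**5. The other moderators (controls coded 0).** Assume motivation acts with log-odds 1.0 per SD on compliance and 0.8 per SD on quitting.

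- If a moderator does not predict compliance and the patch has no effect, adding compliance leaves its interaction essentially unchanged.
- If it does predict compliance (log-odds 0.3 to 0.5 per SD for metabolism, 0.8 for prior NRT), still with no patch effect, the interaction log OR moves by about 0.04 to 0.12.
- If prior NRT lowers compliance by 0.8 and the patch works only through compliance (log-odds 1.2), the prior-NRT interaction OR goes from about 0.85 to about 1.10. Part of that shift is the removal of an effect that runs through compliance.

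**The case against.** The strongest reply is that the trial's result is safe. The primary hypothesis is tested in Step one, before compliance enters. That stands. A reader might infer from a distorted condition effect that the primary comparison is biased; the Analysis Plan does not support that.

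A reader might also infer that Step three as a whole cannot be fitted. That goes too far when controls are coded 0. Software would drop one redundant column, and the 3-HC/cotinine and prior-NRT interactions would still be estimated. Nor are those interactions invalid as a matter of course: they shift only where the moderator predicts compliance, and by an amount that depends on assumptions.

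The aim can fairly be read as a question about smokers who were offered patches. With controls at 0, the Step two compliance coefficient is in effect a comparison within the experimental arm. Subgroup (b), worded around patches that subjects were sent, may be meant for that arm only, with a lead-in drafted for the other subgroups. This is reasonable, and it means an association can be recovered. It does not make that association causal, and it does not rescue the interaction or the Step two condition coefficient.

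Finally, a use variable for both arms could be built from the interview questions on outside NRT. The document does not define compliance that way, and such a variable would still arise after randomisation.

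**Conclusion.** The point holds as a defect of the secondary mediator and moderator analysis and should be fixed. Under the document's own definition, the compliance-by-condition term cannot be estimated with controls at 0. With controls missing, neither condition nor any interaction can be. These results are algebra and need no assumed inputs.

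With controls at 0, the Step two condition coefficient no longer estimates the effect of the offer. Its size cannot be fixed from the document, which gives no compliance rate and no quit rate by compliance. The range of 0.53 to 1.66 against 2.48 rests on the assumed 2% to 6% quit rate in non-compliers, and no single value in it should be read as the expected bias. The interaction step does not test mediation.

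The primary test, the 403 per condition and the 1,000 randomised are unaffected.

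**What to change.** - Remove compliance from Steps two and three.
- Keep only baseline variables as moderators: 3-HC/cotinine ratio, prior NRT use and sex.
- Restrict the compliance analysis and subgroup (b) to the experimental arm, and label the result a non-randomised association.
- Drop the statement that interaction terms test mediation.

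Optionally, add a complier average causal effect with randomised condition as the instrument, as a sensitivity analysis. It would need a stated definition of a complier (if that means the full course, partial users must be assumed to gain nothing), a stated exclusion assumption, and a rule for controls who obtain NRT elsewhere. The exclusion assumption is not automatic: the Control condition section treats a placebo effect as irrelevant to the objective, so an effect of the offer itself is left open. For that reason this analysis should not be required.

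The cost is wording in the Analysis Plan. Sample size, interviews and planned data collection do not change.

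### Agreement between the missing-as-smoker and completer analyses does not show that attrition was non-differential or harmless, so the rule can give false assurance

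*Protocol article*

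**What the plan says.** The Analysis Plan of the protocol article sets out three steps on missing outcomes and one conclusion.

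- Primary handling: "In the primary analyses, subjects lost to follow-up will be assumed to be active smokers".
- A direct check on loss: "we will also conduct a chi-square test to explore whether there is differential loss to follow-up between experimental conditions".
- A second analysis: "Further we will replicate the primary analyses with all subjects with missing data excluded from the analyses".
- The conclusion: if the second analysis and the primary one give the same results, "then we can safely assume that there is no differential attrition between conditions". A parenthesis then weakens this: "or, at least none that impacted on the outcome of the trial".

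The article does not define what counts as the same result. The Power analysis section expects 20% attrition by 6 months and 1,000 randomized, and predicts that "subjects in the control condition will display a 3.7% quit rate and subjects in the experimental condition will display a 8.7% quit rate".

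**The concern.** The rule draws a conclusion about subjects whose outcomes are unknown from two analyses that contain no information on those outcomes. The completer analysis drops the lost subjects; the primary analysis sets them all to smoking. The observed quitters are identical in both, and only the denominators change. Agreement between them is close to automatic when the arms lose similar numbers, so it cannot be evidence that the losses were harmless.

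The stake is the statement that the trial may make about its primary outcome. About 200 of the 1,000 randomized are expected to be lost, against roughly 50 observed quitters at the plan's rates. A report that followed the rule could tell policy makers that attrition had been ruled out as an explanation when it had not been examined.

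**Working it through.** **Inputs from the protocol article.** Quit rates of 3.7% (control) and 8.7% (experimental), 20% overall attrition and 1,000 randomized (Power analysis); half allocated to each arm (Design), so 500 per arm.

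**Assumptions of this check.** The split of loss by arm and the quit rates among lost subjects are not in the article; ranges are shown. P-values are two-sided Pearson chi-square without continuity correction, which is the score test for a logistic regression with one binary term.

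**The plan's own figure.** With p1 = 0.087, p2 = 0.037, two-sided alpha 0.05 and 80% power, the two-proportion formula gives 364 per arm uncorrected and 403 with the continuity correction ("estimate calculated with continuity correction factored in"). The stated 403 is reproduced, and 800/0.8 = 1,000. Nothing below changes it.

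**Step 1: how the two analyses are related.** In each arm let x be observed quitters, n subjects followed and N subjects randomized.

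- Completers: RR = (xE/nE) / (xC/nC).
- Missing-as-smoker: RR = (xE/NE) / (xC/NC).
- Hence RR(missing-as-smoker) = RR(completers) × (nE/NE) / (nC/NC).

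The only link is the ratio of retention. Quitting among the lost appears nowhere.

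**Step 2: does agreement show equal loss?** Assume loss of 15% experimental and 25% control (75 and 125 lost), with 8.7% and 3.7% quitting among those followed.

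| Analysis | Experimental | Control | OR | p |
|---|---|---|---|---|
| Completers | 37/425 | 14/375 | 2.46 | 0.004 |
| Missing-as-smoker | 37/500 | 14/500 | 2.77 | 0.0009 |
| Loss by arm | 75/500 | 125/500 | – | 0.00008 |

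Check of Step 1: 2.33 × 0.85/0.75 = 2.64, and (37/500)/(14/500) = 2.64. Both analyses are significant in the same direction although loss differs by 10 points. With the loss reversed (25% vs 15%) they give 33/375 vs 16/425, p=0.003, and 33/500 vs 16/500, p=0.013. Over assumed gaps of 0 to 20 points in either direction, they part on significance only at 30% experimental vs 10% control (p=0.004 and p=0.052).

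**Step 3: does agreement show that attrition did not affect the outcome?** Assume equal 20% loss, 100 per arm. Observed quitters are 0.087 × 400 ≈ 35 and 0.037 × 400 ≈ 15.

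- Loss by arm: 100 vs 100, p=1.0.
- Completers: 35/400 vs 15/400, RR 2.33, OR 2.46, difference 5.0 points, p=0.003.
- Missing-as-smoker: 35/500 vs 15/500, RR 2.33, OR 2.43, difference 4.0 points, p=0.004.

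All the planned checks pass. Now let no lost experimental subject have quit and vary quitting among the 100 lost controls:

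| Quitters among lost controls | All randomized | OR | p |
|---|---|---|---|
| 0 | 35/500 vs 15/500 | 2.43 | 0.004 |
| 4 (about the 3.7% control rate) | 35/500 vs 19/500 | 1.90 | 0.025 |
| 6 (6%) | 35/500 vs 21/500 | 1.72 | 0.054 |
| 20 (20%) | 35/500 vs 35/500 | 1.00 | 1.0 |

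The rule returns the same verdict on every row, because neither planned analysis nor the loss test uses the second set of quitters.

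**The case against.** Several points on the other side stand.

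- The parenthesis partly withdraws the claim that loss was equal, so Step 2 bears mainly on the stronger form. Step 3 is the answer to the hedged form.
- The planned chi-square test would expose gross imbalance. At 10% vs 30% loss its p-value is about 3e-15, even though both outcome analyses remain significant (39/450 vs 13/350, p=0.005; 39/500 vs 13/500, p=0.0002). What it cannot detect is equal loss with different outcomes.
- A strict reading of sameness might not treat odds ratios of 2.46 and 2.77 as equal. No reading rescues Step 3, where the risk ratios are identical.
- Some features limit arm-specific dropout: controls do not expect patches (Control condition), the honorarium is the same (Design), and interviewers are blind until the primary outcome has been asked (Blinding).
- Further sensitivity analyses may sit in a SAP that is not shown, so their absence is not the complaint. The stated inference is, and a SAP would not make it valid.

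A reader might infer that the rule would certify a biased or false-positive result. The documents do not support that. One can construct a null case in which every check passes: 8% quitting in both arms and quitters retained 95% vs 50% give 401 vs 400 followed (p=0.94), 38/500 vs 20/500 (p=0.015) and 38/401 vs 20/400 (p=0.015). But those retention figures are strong assumptions, and 8% is not the plan's control rate. At a null rate of 3.7% the same retention gives about 18/500 vs 9/500, p=0.08.

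**Conclusion.** The inference is invalid in both its strong and its hedged form. Agreement between the two analyses reflects similar retention and shared quitters; it says nothing about what the lost subjects did. The rule can even declare no differential attrition against the plan's own loss test (p=0.00008 at an assumed 15% vs 25% loss).

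The size of the exposure is moderate. At the plan's rates, with equal 20% loss and no quitting among lost experimental subjects, significance survives if lost controls quit at about the assumed control rate (p=0.025) and is just lost at 6% (p=0.054). Removing the effect altogether needs 20%, which is extreme against 3.7%. These results rest on the assumed loss splits and quit rates among the lost.

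The rule can therefore give false assurance; nothing in the article shows that harmful attrition will happen. Running both analyses is sensible, and the primary test, its handling of missing outcomes and the sample size do not depend on the sentence. It should be corrected, but it does not undermine the primary analysis.

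**What to change.** Delete the sentence containing the rule, or replace it with a statement that agreement between the two analyses is reassuring but does not rule out attrition bias. Keep both analyses and the chi-square test, and interpret the primary result alongside loss by arm.

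Add a sensitivity analysis that varies the quit rate among lost subjects separately in each arm, from all smoking to the observed rate and beyond. Include the adverse corner (experimental lost all smoking, control lost quitting at the observed control rate), and report the tipping point at which the conclusion changes.

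The cost is a change of wording and a short extra analysis on data already held. The conclusion on attrition may become less favourable than the current rule would allow. No change to the primary analysis or to the number randomized is needed.
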